### Sample size

The sample size for this study has been determined based on the continuous primary outcome (walking capacity) using the minimal clinically important change (MCID) of 331 m which represents the MCID at 2 months following nonsurgical treatments according to Carlesso and colleagues [26]. Considering a one-sided significance level of *α* = 0.05, a power of 80%, and an attrition rate of 15%, a total of 66 participants (33 per group) will need to be recruited.

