### Primary outcome

The primary outcome of this study is walking capacity which will be assessed using the Self-Paced Walking Test (SPWT). The SPWT represents the current gold standard for assessing walking capacity in patients with LSS [9, 25]. During this test, participants will be asked to walk freely on a leveled surface at their own pace until they are forced to stop for a minimum of 3 s because of LSS symptoms. The time and distance reached by the participants will be measured. The minimal clinically important change (MCID) reported for the SPWT varies between 319 and 376 m [26]. As patients with LSS causing NC are at higher risk of falls, participants will walk near a ramp and a research assistant will also walk behind the participant during the walking test to assist if needed.

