### Statistical analyses

Baseline characteristics and outcome measures will be summarized with descriptive statistics for each group. Two-tailed independent sample *t* tests will be performed to compare group baseline characteristics. Paired factor analyses using analyses of covariance will be performed for each of the outcome measures (primary and secondary). Such analysis ensures that identified confounding factors do not influence intergroup differences. ANOVAs will be used to compare the evolution of walking capacity over weeks. An intention-to-treat method will be used, and missing data will be replaced using a multiple imputation method. No additional analyses (e.g., subgroup and adjusted analyses) are planned for this study. Statistical analyses will be conducted using SPSS statistical version 26 for the Windows software, and the level of significance will be set at a *p*-value ≤ 0.05.

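### The 80% power behind 66 participants is for a one-sided 5% test, but the planned ANCOVA/ANOVA tests carry no one-sided rule; tested two-sided and unadjusted, power is about 70%

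*Protocol article*

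**What the plan says.** The Sample size section of the protocol article sets out its inputs: "Considering a one-sided significance level of" 0.05, "a power of 80%, and an attrition rate of 15"%, and as the difference to detect a "minimal clinically important change (MCID) of 331 m". The result is that "a total of 66 participants (33 per group) will need to be recruited". No standard deviation is given.

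The Statistical analyses section says "Paired factor analyses using analyses of covariance will be performed for each of the outcome measures (primary and secondary"), adds ANOVAs for walking capacity over the weeks, and closes with "the level of significance will be set at a" p-value of 0.05 or less. The only sidedness named in that section is two-tailed, and it applies to the baseline t tests. The section does not say that the primary p-value will be halved or that a directional contrast will be used.

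The Background and Study design sections state a directional aim: exercise plus education is expected to be superior to education alone.

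**The concern.** A sample size is valid only for the test that will be run. With two arms, the group effect in an ANCOVA is an F test on one degree of freedom. Its p-value equals that of a two-sided t test, so an F test at p ≤ 0.05 puts 2.5% in the direction of benefit. The sample size section spends 5% in that direction.

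Two things are at stake. First, 80% is the figure that justifies the trial's size. If the real figure is lower, a non-significant result will be read as firmer evidence against the exercise program than it is. Second, with the two sections unreconciled, a favourable result with a two-sided p between 0.05 and 0.10 could be called significant by one section and non-significant by the other.

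**Working it through.** **Inputs from the protocol article.** One-sided α = 0.05, power 80%, difference 331 m, attrition 15%, 33 per group (Sample size); 1:1 allocation (Randomization); ANCOVA/ANOVA at p ≤ 0.05 (Statistical analyses).

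**Input not given.** The SD of walking distance. It is back-calculated below only where metres are needed.

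**1. The plan's own figure.** The attrition step is consistent: 28 / 0.85 = 32.9, which rounds up to 33 per group, 66 in total. The 28 completers cannot be reproduced independently without the SD. By the normal approximation, 33 per group comes out one-sided for an SD of 490 to 498 m. It would also come out two-sided for an SD of 435 to 442 m.

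**2. Power if the same comparison is tested two-sided (normal approximation).**
- One-sided 5% with 80% power fixes δ/SE = 1.645 + 0.842 = 2.486 (before rounding of the parts).
- Two-sided at 5%: power = Φ(2.486 − 1.960) = Φ(0.526) = 70.1%.
- Neither the SD nor n enters, so the drop does not depend on the missing SD.

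**3. Noncentral t, 28 completers per arm.**
- 80% power one-sided requires d = 0.673, so the implied SD is 331 / 0.673 = 492 m.
- The same d tested two-sided at 0.05 gives 69.6%.
- If all 33 per arm contributed full information, the same d gives 76.8%. This is the upper limit for what imputation and repeated measurements could preserve without covariate adjustment.

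**4. Effect of adjusting for baseline walking distance.** Adjustment turns d into d / √(1 − r²), where r is the baseline-to-follow-up correlation. The protocol gives no r, so a range is shown (two-sided 0.05, 28 per arm, noncentral t):

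| Assumed r | Power |
|---|---|
| 0 | 69.6% |
| 0.3 | 74% |
| 0.4 | 77% |
| 0.47 | 80% |
| 0.5 | 81% |
| 0.6 | 87% |

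**5. In metres, conditional on the SD of 492 m.** Unadjusted two-sided 80% power needs d = 0.762, that is 0.762 × 492 = 375 m. The Primary outcome section says "The minimal clinically important change (MCID) reported for the SPWT varies between 319 and 376 m", so this is the top of the protocol's own range. At 319 m the power is 66%.

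**6. Size that would restore 80% unadjusted and two-sided.** 36 completers per arm; 36 / 0.85 = 42.4, so 43 enrolled per arm, 86 in total against 66.

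**The case against.** A reader might infer that the trial's power simply is 70%, or that 66 is a miscalculation. The documents support neither.

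- **Sidedness is inferred.** The analysis section never calls the primary test two-sided. The aim is directional, the sample size is openly one-sided, and a two-arm ANCOVA contrast can be tested one-sided at 0.05, which would keep 80%. This stands as a limit on the claim. It does not remove the mismatch: the tests and threshold are written down without a one-sided rule, and their default form is two-sided. Nor is this only a detail left to a separate analysis plan, because the one-sided basis is stated in one section and the tests in the next.
- **ANCOVA may recover the power.** It may, if baseline walking distance is a covariate and the undisclosed SD is an unadjusted one. The plan refers only to identified confounding factors, does not name baseline SPWT, says no adjusted analyses are planned as additional analyses, and takes no credit for adjustment in the sample size. If the SD was already adjusted, the gain cannot be counted again. Neither 70% nor 80% can therefore be asserted for the analysis as it will be run.
- **28 per arm is the pessimistic base.** Intention-to-treat with multiple imputation and five walking tests may retain information from dropouts. This stands, and it caps unadjusted power at about 77%, still short of 80%.
- **The metre figures are soft.** They rest on a back-calculated SD. The fall from 80% to about 70% does not.

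Using an MCID as the target difference is a common choice, is disclosed, and is not part of this point.

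**Conclusion.** The point holds as an inconsistency between two sections, not as an arithmetic error. The stated 80% belongs to a one-sided 5% test; the planned F tests at p ≤ 0.05 are, for two groups, two-sided. Given a two-sided primary comparison, an unadjusted sample-size calculation, and a stated 80% that is correct one-sided, power for the same difference is about 70%, and at most about 77% with no information lost to dropout. A true effect of that size would then be missed about 30% of the time instead of 20%. Baseline adjustment would bring power back to 80% at a correlation of about 0.47, but that correlation is an assumption and the plan does not commit to the adjustment. If a one-sided test is truly meant, the power stands and the false-superiority rate is 5% instead of 2.5%, which the analysis section does not declare.

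**What to change.** Keep 66 participants and align the Sample size and Statistical analyses sections:

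1. State that the primary test is two-sided at 0.05.
2. Restate the power in one of two ways: about 70% for 331 m unadjusted, or the power of a prespecified ANCOVA with baseline SPWT as covariate under a stated and justified correlation (for example about 74% at 0.3, about 81% at 0.5).
3. If a one-sided primary test is intended instead, say so explicitly in Statistical analyses and justify the 5% one-sided error.
4. Report the SD used and whether it is already adjusted for baseline. This makes 66 verifiable and shows whether the adjustment gain can be credited. Until then, figures such as 375 m for 80% power should be labelled as conditional on an SD of about 492 m.

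The cost is wording in two sections and, unless baseline adjustment is credited or a one-sided test is justified, a less favourable stated power. No extra patients or visits are needed.

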### Statistical analyses

Baseline characteristics and outcome measures will be summarized with descriptive statistics for each group. Two-tailed independent sample *t* tests will be performed to compare group baseline characteristics. Paired factor analyses using analyses of covariance will be performed for each of the outcome measures (primary and secondary). Such analysis ensures that identified confounding factors do not influence intergroup differences. ANOVAs will be used to compare the evolution of walking capacity over weeks. An intention-to-treat method will be used, and missing data will be replaced using a multiple imputation method. No additional analyses (e.g., subgroup and adjusted analyses) are planned for this study. Statistical analyses will be conducted using SPSS statistical version 26 for the Windows software, and the level of significance will be set at a *p*-value ≤ 0.05.

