Bove and colleagues reported that patients value individual sessions focused on their specific impairments and limitations as well as specific tips on self-management strategies [18]. In the last few years, RCTs involving patients with LSS causing NC were designed to include education as part of the intervention [19–22]. However, the authors did not describe in detail the content of the education program (i.e., daily living tips to limit pain, information regarding walking and sleeping) nor how it was delivered during the study (e.g., frequency, duration, delivery methods such as individual session or information flyers) making the replication of those studies difficult.

The aim of the proposed protocol is to evaluate the effectiveness of a 6-week specific rehabilitation program combining education and exercises on walking capacity in patients with LSS causing NC. It is hypothesized that a 6-week specific rehabilitation program combining exercises and education will have a superior effect on walking capacity than education alone.

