### Data collection

Participants will be evaluated five times during the study (baseline, week 2, week 4, week 6, and week 12). Each assessment will include both patient-reported outcome measures (PROMs) and objective physical measures. All assessments will be conducted at the UQTR biomechanics laboratory. The data collection process is synthesized in Table 1. All participants will be called for a reminder before each assessment.

**Table 1 Tab1:** Data collection

	Measures	Baseline assessment	Week 2 assessment	Week 4 assessment	Week 6 assessment	Week 12 assessment
Baseline measurements	Sociodemographic data and physical examination	X	–	–	–	–
Primary outcome	SPWT	X	X	X	X	X
Secondary outcomes	NRS for leg pain intensity	X	X	X	X	X
	NRS for back pain intensity	X	X	X	X	X
	Leg pain dominance	X	–	–	–	–
	FC-SSSQ	X	–	–	X	X
	FC-CPSES	X	–	–	X	X
	FC-HADS	X	–	–	X	X
	QAPPA	X	–	–	X	X
	Gait pattern characteristics	X	X	X	X	X
	SPPB	X	–	–	X	X
	Global perceived change	–	X	X	X	X

*SPWT* Self-Paced Walking Test, *NRS* Numerical Rating Scale, *FC-SSSQ* French-Canadian adaptation of the Swiss Spinal Stenosis Questionnaire, *FC-CPSES* French-Canadian Chronic Pain Self-Efficacy Scale, *FC-HADS* French-Canadian adaptation of the Hospital Anxiety and Depression Scale, *QAPPA* Questionnaire d’activité physique pour les personnes âgées [Physical Activity Questionnaire for the Elderly], *SPPB* Short Physical Performance Battery

During the baseline assessment, participants will first complete a series of questionnaires and undergo a standardized physical examination. The questionnaires will include measures of age, sex, height, weight, leg pain dominance, and number of falls in the past 6 months. Participants will also be asked about the presence of comorbidities known to have a negative influence on walking capacity as well as previous conservative treatment (e.g., injection, manual therapy). The physical examination will include the assessment of lower limb dermatomes and myotomes as well as pallesthesia and osteotendinous reflexes (to document the absence of peripheral neuropathy).

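### Walking capacity has two planned analyses (ANCOVA and ANOVA over weeks) and five visits, and the protocol does not say which analysis or visit decides the trial

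*Protocol article*

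**What the plan says.** All references are to the protocol article.

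- **Hypothesis (Background).** The programme of exercise plus education "will have a superior effect on walking capacity than education alone". This is a comparison between arms.
- **Outcome (Primary outcome).** "The primary outcome of this study is walking capacity which will be assessed using the Self-Paced Walking Test (SPWT". Both time and distance are recorded.
- **Visits (Data collection).** "Participants will be evaluated five times during the study (baseline, week 2, week 4, week 6, and week 12". Table 1 schedules the walking test at all five.
- **First analysis (Statistical analyses).** "Paired factor analyses using analyses of covariance will be performed for each of the outcome measures (primary and secondary". Its stated aim is between-group: "Such analysis ensures that identified confounding factors do not influence intergroup differences". The covariates and the visit are not given.
- **Second analysis (same section).** "ANOVAs will be used to compare the evolution of walking capacity over weeks". No group factor, interaction or contrast is given.
- **Missing data (same section).** "An intention-to-treat method will be used, and missing data will be replaced using a multiple imputation method".
- **Adjustment (same section).** "No additional analyses (e.g., subgroup and adjusted analyses) are planned for this study".
- **Significance (same section).** One threshold, p ≤ 0.05, covers all tests.
- **Sample size.** A single difference of 331 m, one-sided α 0.05, 80% power and 15% attrition give 66 patients (33 per group).

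**The concern.** The article commits itself to two methods for its single primary outcome and gives no rule for choosing between them. They need not agree, and only one kind of result answers the hypothesis.

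- If the ANOVA tests time, or is run within each arm, it asks whether patients change. Both arms receive education and usual care, so both may improve. A significant result would then say nothing about exercise.
- If it is a group-by-time test over five visits, it has 4 degrees of freedom and does bear on the arms. The F statistic still gives no difference in metres at any visit, whereas the sample size rests on exactly one such difference.

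The ANCOVA is aimed at the right question, but it could be run at any of four follow-up visits. The 331 m figure does not settle which, because it is described as a two-month value and two months falls between the week-6 and week-12 assessments. A choice of method and visit made after the data are seen would inflate the false-positive rate. Discordant results would have no agreed reading.

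**Working it through.** **1. The plan's own figure.** No SD is stated, so 66 can be reproduced only by solving for it. With n per arm = 2(1.645 + 0.842)²(SD/331)², an SD of 498 m gives 2 × 6.18 × 2.264 ≈ 28. Then 28/0.85 = 32.9, so 33 per arm and 66 in total. One-sided, SDs of 490 to 498 m give exactly 66. Below I use SD 498 m and 28 evaluable per arm. The SD, the correlations and the effect patterns are assumptions; the article gives none of them.

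**2. A time effect is not a test of the arms.** Suppose there is no arm difference and both arms improve gradually by 200 m, reached at week 6 and held at week 12. The visit means are 0, 66.7, 133.3, 200 and 200, and the squared deviations from their mean sum to 30,222. The non-centrality is λ = 2n × 30,222 / [SD²(1 − ρ)]. At ρ = 0.6 this is 56 × 30,222 / (248,004 × 0.4) = 17.1, and with F(4, 216) the test is significant 92% of the time. At ρ = 0.5 and 0.7 the figures are 85% and 98%.

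**3. False-positive rate when the choice is open.** As a yardstick, two independent tests at 5% would give 1 − 0.95² = 9.8%, and five (four visits plus the ANOVA) would give 1 − 0.95⁵ = 22.6%. These tests are correlated, so the true rates are lower. I simulated trials with no arm difference, complete data and two-sided 5% tests: group-by-time ANOVA with Greenhouse-Geisser correction, and ANCOVA on baseline at each follow-up visit (10,000 runs per row).

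| Assumed correlation | ANOVA or week-6 ANCOVA | ANOVA or ANCOVA at any visit |
|---|---|---|
| Equal, 0.5 | 8.8% | 18.5% |
| Equal, 0.6 | 8.1% | 17.4% |
| Equal, 0.7 | 8.2% | 17.3% |
| Autoregressive, 0.9 per 2 weeks | 8.6% | 16.6% |

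The multivariate form of the ANOVA gives 8.6–9.1% and 16.7–18.6%. In round terms the rates are 8–9% and 16–19%.

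**4. Discordance under a real effect.** With an effect that grows to 331 m at week 6 and is held at week 12, the group-by-time ANOVA and the week-6 ANCOVA disagree on significance in roughly 12–27% of trials over the same correlations. A repeat run agreed to within about one point for the corrected test.

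**5. Relative power, two-sided 5%, equal correlations.** For ANCOVA the residual SD is 498√(1 − ρ²). At ρ = 0.6 this is 398 m, so the non-centrality is 331 / (398 × √(2/28)) = 3.11 and power is 86%. For the group-by-time test, λ = (n/2)Σ(d_t − d̄)² / [SD²(1 − ρ)].

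| Test and effect pattern | ρ = 0.5 | ρ = 0.6 | ρ = 0.7 |
|---|---|---|---|
| Week-6 ANCOVA | 0.805 | 0.863 | 0.928 |
| Group-by-time: gradual, held | 0.671 | 0.780 | 0.896 |
| Group-by-time: gradual, half lost by week 12 | 0.521 | 0.629 | 0.771 |
| Group-by-time: weeks 6 and 12 only | 0.880 | 0.945 | 0.987 |

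The ordering depends on the pattern. Under the autoregressive correlation the multivariate form beats the ANCOVA in three of five patterns examined (about 0.995–0.999 against 0.94) and loses in the two gradual ones (0.736 and 0.786 against 0.94).

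**The case against.** The strongest case against is that the right analysis is already in the plan. ANCOVA is promised for the primary outcome with a between-group purpose, and a description of the time course beside it is ordinary practice. The article nowhere says that the ANOVA displaces the ANCOVA, that it is omnibus-only, or that it assumes equal correlations. Factors, contrasts and corrections are also details that an article may leave to the full protocol or analysis plan.

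Much of this stands, and it rules out three stronger readings that a reader might infer.

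- *That the ANOVA costs the trial power.* The 81–93% power of the week-6 contrast belongs to the planned ANCOVA, provided baseline distance is a covariate. The group-by-time test is weaker under some effect patterns and stronger under others.
- *That a mixed model must replace the plan.* With complete data it gives essentially the same contrast as ANCOVA. ANCOVA with multiple imputation is a legitimate approach under missing-at-random.
- *That the ANOVA is the primary test.* The text does not say so.

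What does not fall away is the choice itself. The missing ANOVA details are not the finding. The article states two analyses of one primary outcome over several visits at one significance level, and ranks neither. If an unseen analysis plan already ranks them, the point is met by bringing that sentence into the article's text.

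**Conclusion.** The point holds as a matter of an unranked primary analysis, not of lost power. Two parts need no assumed figures: nothing in the article says which method or visit decides, and a time-only or within-arm ANOVA cannot answer the between-arm hypothesis. The size of the risk does rest on assumptions: SD 498 m (back-solved), 28 evaluable per arm, complete data, two-sided 5% tests and correlations as in the working. On these, the false-positive rate is about 8–9% if either test may be claimed and about 16–19% if any visit may be. Results would be discordant in roughly 12–27% of trials under a gradual 331 m effect. These rates describe what the wording permits; nothing suggests that the investigators intend to select.

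The sentence excluding adjusted analyses adds a smaller inconsistency. Taken literally it conflicts with ANCOVA. It may mean none beyond the ANCOVA, but it should say so.

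**What to change.** 1. Name one primary analysis: the between-arm difference in Self-Paced Walking Test distance at one pre-stated visit, for example week 6 as the end of the programme, with a 95% CI. Distance matches the 331 m basis of the sample size.
2. Obtain it from an ANCOVA adjusted for baseline distance and the four minimisation factors (smoking, diabetes, chronic obstructive pulmonary disease, stroke), with the planned intention-to-treat multiple imputation. A baseline-adjusted repeated-measures mixed model reporting the same contrast would be equally acceptable.
3. Label the ANOVA over weeks and the ANCOVA results at the other visits as supportive. State that they do not decide the trial, and that change over time within an arm is not evidence of a difference between arms.
4. Reword the exclusion of adjusted analyses so that it covers only analyses beyond the specified ANCOVA.

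The cost is a few sentences, settled before group-level results are seen. The data, visits, sample size and software stay the same.

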### Adverse events and harms

All adverse events (minor or major) associated with both intervention and usual care will be monitored using open-ended questions. Adverse events are defined as any undesirable experience occurring to a participant, with or without relation to the intervention. These undesirable experiences include an increase in back or leg pain intensity and claudication discomfort. Each adverse event reported by participants throughout the study will be considered and discussed with the research team. Adverse events that are associated with an increase in disability will be reported to the ethics committees. There is no anticipated harm and compensation for trial participation.

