#### Eligibility criteria

To be eligible, participants must meet the following inclusion criteria: (1) being at least 50 years old; (2) having a degenerative central LSS alone or in combination with other LSS types (e.g., foraminal, lateral recess) and/or a spondylolisthesis affecting one or multiple vertebral levels, confirmed by clinical history, physical examination, and proper imaging (MRI and/or CT scan); (3) having NC associated with LSS; (4) with a duration of signs and symptoms of at least 3 months; (5) being able to walk at least 20 m without walking aid, but not being able to walk continuously for 30 min; (6) being willing to attend 3 intervention sessions per week over a period of 6 weeks; (7) being able to speak and understand French; and (8) being able to provide informed written consent. Participants with congenital LSS, traumatic and pathological causes of LSS, symptomatic osteoarthritis (hip or knee) causing limited walking capacity, a neurological disease affecting walking capacity such as Parkinson, uncontrolled diabetes, heart failure, intermittent claudication of vascular origin, impaired cognitive capacity, and history of back or lower extremities surgery in the past 3 months will be excluded.

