### Interventions

#### Intervention group

Participants allocated to the intervention group will receive a 6-week specific rehabilitation program which includes training and education sessions. The one-on-one training sessions will be composed of specific exercises to be performed 3 times per week under the supervision of a certified kinesiologist. Of the three training sessions, one will take place at UQTR’s outpatient clinic while the other two will take place online using a telecommunication platform (e.g., Zoom or Google Duo, depending on the participant’s preference) allowing for remote supervision of the training by the certified kinesiologist. Instructions regarding the selected telecommunication platform will be provided to the participants. Education will take place at week 2 and week 4 with the researcher responsible of the assessments. The presence to exercises and education sessions will be monitored by the responsible research team member (CT for exercises and MH for education).

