### Data management

The researchers shall fill in data to the data collection sheet accurately, completely, and timely based on original observations. MH will be responsible to fill in data collection sheets during each evaluation, and CT will be responsible to fill in data collection sheets during each intervention. Researchers are responsible for ensuring the accuracy of all data entered and recorded. All data collected during this study are totally confidential and will never allow participant identification. Confidentiality will be assured by replacing the participants’ names by an alphanumeric code. The data collected will be stored under lock and key in the evaluation or intervention room (paper documents) or on a secure network with both network and electronic document access protected by passwords under the responsibility of the Chaire de recherche internationale en santé neuromusculosquelettique at the Université du Québec à Trois-Rivières. Only the research members will have access to these data. All of them have signed a confidentiality agreement. All data will be destroyed 5 years after the end of the study. For monitoring and control purposes, research files may be consulted by a person mandated by the CIUSSS MCQ Research Ethics Board or by a person mandated by authorized public agencies. All these persons and organizations adhere to a confidentiality policy. Full name, contact information, and the start and end date of participation for each participant in the project will be kept for 1 year after the end of the project in a separate directory maintained by the researcher responsible (MH) for this research project. For randomization purposes, a research assistant will have access to baseline data. This research assistant has also signed a confidentiality agreement.

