### Composition of the coordinating center and trial steering committee and plans for auditing trial conduct

The coordinator of the study is MH. She is responsible for all aspects of the local organization including identifying potential recruits and taking consent from participants. In addition to MH, CEC is responsible for the identification of potential recruits in the regional hospital outpatient clinic. CT (certified kinesiologist) is the supervisor of each session of exercises for the intervention group. The project is supervised by MD and AAM. Both are professors at UQTR and are supervising MH’s doctoral studies. The local Trial Steering Committee is composed of MH, CT, CEC, AAM, and MD. The team discussed the test protocols, the intervention content, and the related materials together. The committee will meet each month throughout the study. If there is any modification to the protocol that needs to be done or if there is any adverse event, the TSC will discuss the situation as soon as possible and will inform the research ethic committee. The monitoring will be conducted by the principal investigator of the study each month as an audit of trial conduct. There is no stakeholder and public involvement group for this study.

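### The article gives two conflicting rules for informing the ethics committee of adverse events; separately, a pooled count of events by arm would be open to ascertainment bias

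*Protocol article*

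**What the plan says.** Two sections of the protocol article state when the ethics committee hears of an adverse event.

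- *Adverse events and harms*: "Adverse events that are associated with an increase in disability will be reported to the ethics committees".
- *Composition of the coordinating center and trial steering committee and plans for auditing trial conduct*: "if there is any adverse event, the TSC will discuss the situation as soon as possible and will inform the research ethic committee".

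The definition that both rules rely on is wide: "Adverse events are defined as any undesirable experience occurring to a participant, with or without relation to the intervention". The same section expressly includes worsening back or leg pain and claudication discomfort.

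On collection, the article says: "All adverse events (minor or major) associated with both intervention and usual care will be monitored using open-ended questions". It adds that each event a participant reports at any time in the study will be considered and discussed with the team. The *Data management* section says that the exercise supervisor "will be responsible to fill in data collection sheets during each intervention". Only the exercise arm has such sessions.

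**The concern.** There are two separate issues.

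The first is oversight. A team member who works from the adverse events section would pass on events linked to increased disability. One who works from the steering committee section would pass on every event. In this population a transient rise in leg pain meets the definition of an adverse event, so the two readings differ for ordinary events and not just for rare ones.

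The second is description of harms by arm. Events enter the record when participants mention them, and one arm is seen far more often than the other. With an open-ended question and a definition that takes in short-lived symptoms, more contact gives more chances to mention something. A pooled tally could then make the exercise programme look more harmful than it is, because minor events in controls go unmentioned.

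**Working it through.** **Reporting rules side by side**

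| Event | Adverse events and harms | Steering committee section |
|---|---|---|
| With increased disability | Reported | Reported |
| Transient pain flare, no added disability | Not among those named for reporting | Reported |
| Fall without added disability | Not among those named for reporting | Reported |

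The rules agree on the first row only.

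**Scheduled contacts after baseline**

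The plan gives no contact total to reproduce, so the count is built from its parts.

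- Sessions per week, exercise arm only: 3 (*Intervention group*: "specific exercises to be performed 3 times per week under the supervision of a certified kinesiologist").
- Duration: 6 weeks (*Eligibility criteria*: "being willing to attend 3 intervention sessions per week over a period of 6 weeks").
- Assessments in both arms: 5, of which 4 follow baseline (*Data collection*: "Participants will be evaluated five times during the study (baseline, week 2, week 4, week 6, and week 12").
- Education: two sessions in both arms, held within the week 2 and week 4 assessments (*Education* and the control group section), so no further contacts.

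Exercise arm: 3 × 6 + 4 = 22. Control arm: 4. Ratio 22 / 4 = 5.5.

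Variants:

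- Through week 6 only: 18 + 3 = 21 against 3, ratio 7.
- Counting the reminder call before each follow-up assessment, made in both arms: 22 + 4 = 26 against 4 + 4 = 8, ratio 3.25.

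**How large the distortion could be**

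The documents give no figure for recall, so this is an illustration under stated assumptions:

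- true event rates are equal in the two arms and uniform over days 0 to 42;
- an event can be reported only at the next contact;
- the probability of reporting is 0.5^(gap in days / h), where h is the recall half-life;
- control contacts fall on days 14, 28, 42 and 84;
- the exercise arm has those contacts plus three sessions in each week (days 1, 3 and 5 of the week).

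Capture is the mean of that probability over the 43 days. For controls with h = 3, the gaps run from 13 down to 0 three times, plus one gap of 14. The sum is 3 × (1 − 0.5^(14/3)) / (1 − 0.5^(1/3)) + 0.5^(14/3) ≈ 14.0, and 14.0 / 43 ≈ 0.33.

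| Half-life h (days) | Exercise | Control | Ratio |
|---|---|---|---|
| 3 | 0.88 | 0.33 | 2.71 |
| 7 | 0.95 | 0.56 | 1.69 |
| 14 | 0.97 | 0.73 | 1.32 |
| 28 | 0.99 | 0.85 | 1.16 |

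Ratios are taken before rounding. The direction is the same throughout; the size depends on the assumed recall.

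**After the change**

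If the comparative count rests on the shared assessments, it has 4 occasions against 4.

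**The case against.** On the reporting rules, the adverse events section does not say that only disabling events are reported, and the broader rule contains the narrower one. Staff who followed both would report everything. That is a fair reading of the words, but naming one class of events as those to be reported has no purpose if all are. A reader cannot tell from the article which rule governs, so the conflict stands.

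On ascertainment, several objections carry weight.

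- The article states no between-arm test of adverse events. The *Statistical analyses* section covers the primary and secondary outcomes, and adverse events are neither. The point therefore applies to any pooled description by arm, not to a planned test.
- The 22 contacts are opportunities. The article does not say that the open-ended question is asked at exercise sessions, or that the session sheets record adverse events. When and by whom the question is asked may stand in a fuller document, and its absence here is not the finding. What the article does say is that events count whenever participants report them.
- An open question at a visit can cover the time since the last one, which would shrink the imbalance. The lower end of the range reflects this.

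A reader might infer that the arms cannot be compared for harms at all. The documents do not support that: both arms share four identical follow-up assessments, and a comparison confined to them is sound. A reader might also infer a doubling of apparent events, because the exercise arm is seen in 6 of 6 programme weeks and controls in 3 of 6. That holds only if an event is reported solely when the patient is seen in the same week, which nothing in the documents establishes.

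Nor does the reporting conflict bear on the comparison. All events, minor or major, are to be monitored and discussed whichever rule governs notification.

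**Conclusion.** The point holds as two separate findings.

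First, the article contains two conflicting rules for informing the ethics committee. An event without added disability is reportable under the steering committee section but is not among those that the adverse events section says will be reported. The passages must be reconciled, and this review takes no position on which rule is right.

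Second, with 22 post-baseline contacts against 4, any pooled between-arm description of adverse events is open to ascertainment bias, probably towards more recorded events in the exercise arm. The contact count follows from the article. The size of the bias does not: about 1.2-fold to 2.7-fold is what equal true rates would produce during the programme under assumed recall half-lives of 28 down to 3 days.

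Both should be corrected, but neither touches the primary analysis or the sample size.

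**What to change.** Reconcile the two sections into a single rule for informing the ethics committee, and state it in the same terms in both places.

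For collection, ask the same open-ended question, covering the time since the last visit, at weeks 2, 4, 6 and 12 in both arms. Base any between-arm comparison on those answers. Record the source of each event (assessment or exercise session), so that events first reported at sessions are still reported in full, in a separate listing.

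The cost is protocol wording, one standard question at visits already scheduled and one source field on the form. The downside is small but real: events mentioned only at an exercise session do not enter the comparative count. Some of these will bear directly on the safety of the exercises, which is why the separate listing must be complete.
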